### Analysis

Statistical analysis of the quantitative elements of the trial is the responsibility of the LICTR statisticians. The analysis plan outlined in this section will be reviewed, and a detailed statistical analysis plan will be written and approved, before any formal analyses are undertaken. Statistical analyses will be carried out by the ITT principle, and statistical significance will be assessed at the two-sided 5% significance level. The ITT population is defined as analysis according to the randomisation and regardless of compliance with the protocol or withdrawal from the trial.

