#### Primary analysis

The primary outcomes associated with enrolment or attrition will be compared between the intervention and control arms through a cluster-level analysis, using a weighted *t* test of cluster-level proportions and a two-stage process to adjust for covariates [55]. Intervention effects and corresponding 95% confidence intervals will be presented. As part of a sensitivity analysis, the reliability of random effects logistic regression will also be investigated.

In the primary analyses, missing data will be assumed to be missing completely at random; that is, analyses will be performed using complete cases (including those where sufficient item-level data exists). The extent of unit non-response (data missing from a whole course) will be assessed, and the reason for missingness and the missing data mechanism will be investigated.

A sensitivity analysis accounting for all participants in the ITT population assuming data missing at random, using multiple imputation, will be performed, and potential predictors of missingness will be investigated. The number of imputations will be determined using Bodner rule of thumb, where number of imputations is similar to the percentage of cases that are complete [56].

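### The rule for the number of imputations is stated backwards, tying it to the percentage of complete rather than incomplete cases (minor)

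*Protocol article*

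**What the plan says.** The protocol article, Primary analysis, treats missing data in two steps.

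- The primary comparison uses complete cases: "In the primary analyses, missing data will be assumed to be missing completely at random".
- A second analysis relaxes that assumption: "A sensitivity analysis accounting for all participants in the ITT population assuming data missing at random, using multiple imputation, will be performed".

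For the second step the number of imputations is fixed by a named rule: "The number of imputations will be determined using Bodner rule of thumb", glossed as "where number of imputations is similar to the percentage of cases that are complete".

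No numerical m, no minimum m and no expected missing-data rate is given; the text says only that "The extent of unit non-response (data missing from a whole course) will be assessed". No other section restates or corrects the rule. The opening of the Analysis section adds that the outline will be reviewed and that "a detailed statistical analysis plan will be written and approved, before any formal analyses are undertaken".

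**The concern.** Multiple imputation replaces missing values by random draws, so a pooled result carries simulation noise that depends on the seed. The noise grows with the amount of information missing and falls as more imputations are run. A rule that sets m from the data should therefore call for more imputations when more is missing. The rule as worded does the opposite: 95% complete data would get about 95 imputations and 20% complete data about 20.

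At stake is the reproducibility of the analysis that the protocol sets against its assumption of data missing completely at random. The rule makes that analysis noisiest when missingness is heaviest. This is a stated operating rule that points the wrong way, not a detail left to a later document, and it could be carried into the analysis plan unchanged.

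**Working it through.** The plan gives a rule but no value of m, so there is no figure to reproduce. The check compares the rule as written with the same rule reversed.

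**Inputs**

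- Rule as written (Primary analysis): m = percentage complete = 100 − p, where p is the percentage of incomplete cases.
- Reversed rule: m = p.
- Missing rate: not given, so p is varied from 5% to 90%.
- Assumption: the fraction of missing information, g, equals p/100.

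**Formulas**

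Under Rubin's rules the total variance is W + (1 + 1/m)B, with W the within-imputation and B the between-imputation variance. The simulation variance of the pooled estimate is B/m. With g approximately B/(W + B):

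- simulation error of the pooled estimate, relative to its standard error ≈ √(g/m)
- efficiency relative to unlimited imputations = 1/(1 + g/m)

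**Results**

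| Incomplete | m, as written | Error / SE | Efficiency | m, reversed | Error / SE | Efficiency |
|---|---|---|---|---|---|---|
| 5% | 95 | 0.02 | 0.9995 | 5 | 0.10 | 0.990 |
| 20% | 80 | 0.05 | 0.998 | 20 | 0.10 | 0.990 |
| 40% | 60 | 0.08 | 0.993 | 40 | 0.10 | 0.990 |
| 50% | 50 | 0.10 | 0.990 | 50 | 0.10 | 0.990 |
| 60% | 40 | 0.12 | 0.985 | 60 | 0.10 | 0.990 |
| 70% | 30 | 0.15 | 0.977 | 70 | 0.10 | 0.990 |
| 80% | 20 | 0.20 | 0.962 | 80 | 0.10 | 0.990 |
| 90% | 10 | 0.30 | 0.917 | 90 | 0.10 | 0.990 |

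For example, at 80% incomplete: √(0.8/20) = 0.20 as written and √(0.8/80) = 0.10 reversed.

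**Why the pattern is general**

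The reversed rule gives √(g/(100g)) = 0.10 at every missing rate. The written rule gives √(g/(100(1 − g))) = 0.10 × √(g/(1 − g)), which exceeds 0.10 only when g is above 0.5.

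**Sensitivity to the assumption on g**

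If the imputation model has good predictors, g is smaller than p/100 and both error columns shrink. Their ratio does not change, because it equals √(p/(100 − p)) whatever g is: √(60/40) = 1.22 at 60% incomplete and √(80/20) = 2 at 80%. The crossing point stays at 50% incomplete.

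**The case against.** The case for leaving the sentence alone has four parts.

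1. *Nothing primary depends on it.* The rule governs one sensitivity analysis, and the primary comparison uses complete cases. This stands.
2. *In the lower range the written rule is the safer one.* At 30% incomplete it gives m = 70 and an error of √(0.3/70) = 0.065, against 0.10 reversed. This stands; below 50% the only cost is computing time.
3. *Even the bad cases are mild.* At 80% incomplete the efficiency is 0.962, which corresponds to a standard error about 2% wider than with unlimited imputations (√1.04 = 1.02). There is no bias. This stands too, although a seed-dependent shift of 0.20 standard errors could still be noticed if a result were near a threshold.
4. *The analysis plan can put it right.* The outline is to be reviewed before any formal analysis. That limits the practical risk but does not make the sentence correct.

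A reader might infer something stronger: that heavy missingness is to be expected here because about half of the 144 centres may have no follow-up course. The Background gives over 150 programmes a year in 32 local authorities. Pro rata for 24 authorities that is 150 × 24/32 = 112.5, and two terms out of an assumed three give 75, or 75/144 = 52% of centres if none ran two.

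The documents do not support that inference. The 150 is a lower bound, and the even spread over three terms is assumed. The exclusion criteria remove centres with no programme planned in the trial period. The protocol describes unit non-response as data missing from a whole course, and does not say that a centre running no course is an incomplete case to be imputed. Even if the figure were accepted, it would show no harm: at 48% incomplete the written rule gives m = 52 and the reversed rule m = 48.

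**Conclusion.** The rule is wrong as written: m falls as missingness rises, whereas constant simulation error requires it to rise. This follows from the variance formula for multiple imputation, without recourse to the cited source. A slip of one word is the likely cause.

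The point is minor. Against the 0.10 benchmark that the reversed rule holds, the shortfall begins only above 50% incomplete cases. The documents give no expected missing rate and so do not show that the trial would reach that range. The sizes quoted take the fraction of missing information as equal to the fraction of incomplete cases, and they measure noise in the pooled estimate relative to its standard error. They are not the run-to-run spread of the test statistic, which also varies through the estimated standard error.

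**What to change.** In Primary analysis, change *complete* to *incomplete* in the gloss on the rule of thumb, and carry the corrected wording into the statistical analysis plan. Add a minimum, for example: m is the larger of 20 and the percentage of incomplete cases.

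The minimum is a judgement; the protocol does not supply it, and the reversed rule already holds the error at 0.10. Its purpose is to avoid a very small m when little is missing. At 5% incomplete the reversed rule alone gives m = 5, so the between-imputation variance would rest on 4 degrees of freedom. With m = 20 the simulation error there is √(0.05/20) = 0.05.

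The cost is one word and one clause. Nothing in the design, the data collection or the primary analysis changes, and the correction can be made before any analysis is run.

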#### Secondary analysis

Adherence to HENRY programme content and the impact of the HENRY optimisation on parenting and family health will be analysed using a cluster-level analysis of either proportions or means, depending on the outcome, as described for the primary analysis. As part of sensitivity analyses, the degree of clustering at each level of the data structure, and the reliability of two-level (parents nested within centres or local authorities) and three-level (parents nested within centres within local authorities) random-effects models will also be investigated. The proportion of centres achieving combined enrolment, attrition and parent adherence will be analysed using the same methods described for the primary outcomes. The longitudinal impact of the intervention on parental engagement will be analysed among those local authorities providing data for more than one programme per centre at follow-up, using logistic regression with random effects adjusting for the time point of the programme.

Appropriate scoring manuals will be followed, and missing items within individual outcome measures will be treated according to instructions for that particular measure. For all other outcomes (without instructions for dealing with missing data), half rule will be used, substitution of the mean of the answered questions for that specific subscale for the missing responses as long as at least half the questions are answered [57]. If more than 50% of the items are missing, the outcome will be assigned as missing.

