## Methods/design

### Design

This study is a two-arm, multi-centre cRCT across 24 local authorities (local governments) (supporting approximately 144 children’s centres) in the United Kingdom to determine the effectiveness and cost-effectiveness of an optimisation intervention to promote parent engagement in the HENRY programme compared with standard HENRY practice (Fig. 1). Although the children’s centres deliver the HENRY programme, owing to the multi-component and interactive nature of the optimisation intervention, local authorities will be the units of randomisation (i.e., clusters) to prevent contamination between the randomised groups. Outcomes will be assessed through routinely collected data available for each HENRY programme at the parent and children’s centre levels. Information on commissioners’ willingness to pay (within local authorities) related to the optimisation intervention will be elicited. A process evaluation will be conducted alongside the cRCT in accordance with the MRC guidance on evaluating process in complex interventions [19].

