### Sample size

We assumed that 25% of the 32 local authorities currently running HENRY will not be eligible or will opt out of the study, leaving 24 local authorities (12 per arm). Power calculations for this fixed sample size (with all eligible centres in the United Kingdom invited to take part) were therefore conducted to examine anticipated power for various intervention effects, at the 5% significance level, in each of the primary outcomes and for the composite endpoint (enrol at least eight parents per programme and retain ≥75% of parents attending five of eight sessions) (see Table 1 for scenarios). On the basis of data from previous HENRY programmes (all terms in 2014), we assumed an average of 6 children’s centres per local authority providing a total of 144 children’s centres (72 per arm), an intra-cluster correlation coefficient (ICC) between 0.05 and 0.1, a coefficient of variation in cluster size of 0.54, and the following estimates of the outcomes in the control sites (HENRY alone): 55% of centres will enrol at least eight parents per programme; 50% of centres will retain ≥75% of parents attending five of eight sessions; and 25% of centres will enrol at least eight parents per programme and retain ≥75% of parents attending five of eight sessions. Thus, with the anticipated number of centres (24 local authorities, 144 children’s centres), we will have at least 80% power to detect meaningful improvements in differences of between 25% and 30% in either of the primary endpoints or the composite endpoint at the 5% significance level, assuming the ICC is no greater than 0.05.

**Table 1 Tab1:** Power calculations for enrolment and attrition endpoints for various estimates of the intervention effect and a fixed sample size of 144 children’s centres in 24 local authorities

Outcome in the control	Percentage point increase in intervention	Power for ICC = 0.1	Power for ICC = 0.05
Enrolment (≥8 parents per programme)			
55%	5%	6%	7%
	10%	15%	18%
	15%	29%	35%
	20%	49%	58%
	25%	70%	79%
	30%	87%	93%
Attrition (≥75% of parents attending five of eight sessions)			
50%	5%	6%	7%
	10%	15%	17%
	15%	28%	34%
	20%	47%	55%
	25%	67%	76%
	30%	84%	91%
Enrolment and attrition (at least eight parents per programme and 75% of parents attending five of eight sessions)			
25%	5%	7%	8%
	10%	17%	19%
	15%	31%	37%
	20%	49%	58%
	25%	67%	76%
	30%	82%	89%

*ICC* Intra-cluster correlation coefficient

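### One of the three random-effects structures named as sensitivity analyses (parents within centres only) omits the randomised local authority and should not be used to estimate an arm effect

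*Protocol article*

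**What the plan says.** The Design section of the protocol article fixes the allocation level: "local authorities will be the units of randomisation (i.e., clusters) to prevent contamination between the randomised groups". The Sample size section plans on "leaving 24 local authorities (12 per arm"), on "an average of 6 children’s centres per local authority providing a total of 144 children’s centres (72 per arm"), on "an intra-cluster correlation coefficient (ICC) between 0.05 and 0.1", and on "a coefficient of variation in cluster size of 0.54". Centre results within one authority are therefore assumed to be correlated.

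Under Secondary analysis, adherence and the parenting and family-health outcomes are to be compared by the same cluster-level approach as the primary outcomes. The same paragraph then lists sensitivity work: how much clustering exists at each level, and how reliable several random-effects models are. Two kinds are named:

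- "two-level (parents nested within centres or local authorities"), which covers two structures;
- a three-level model with parents in centres in authorities.

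Three structures are thus in play, and two of them carry the authority. Under Analysis, "statistical significance will be assessed at the two-sided 5% significance level".

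**The concern.** A model with parents in centres and nothing above the centre treats about 144 centres as independently allocated. Only 24 units were allocated. Centres in the same authority share both the arm and whatever makes that authority different. The model attributes that shared variation to chance differences between centres, averages it over too many units, and reports an arm effect with too small a standard error. This follows from the design and holds whenever authority-level variance is above zero, which the sample size calculation itself assumes for the engagement outcomes.

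At stake is the usefulness of one sensitivity analysis. If an arm effect from the centres-only model were set beside the cluster-level result, it would tend to look more precise for a reason unrelated to robustness. Agreement or disagreement between the two would be hard to interpret.

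**Working it through.** **Inputs from the protocol (Sample size, Analysis).** 24 authorities, 12 per arm; mean 6 centres per authority, 72 centres per arm; coefficient of variation of cluster size 0.54; ICC 0.05 to 0.1; two-sided 5% level.

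**Step 1: reproduce the plan's own figures.** The design effect is

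DE = 1 + ((1 + CV²) × m − 1) × ICC.

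With CV² = 0.2916 and m = 6, (1.2916 × 6) − 1 = 6.7496. So:

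- ICC 0.05: DE = 1 + 6.7496 × 0.05 = 1.337, effective centres per arm 72/1.337 = 53.8;
- ICC 0.10: DE = 1 + 6.7496 × 0.10 = 1.675, effective centres per arm 72/1.675 = 43.0.

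A two-proportion normal power formula with these effective sizes gives, for enrolment 55% against 80%, 79.9% and 70.3% (Table 1: 79% and 70%). For attrition 50% against 75% it gives 77.2% and 67.3% (Table 1: 76% and 67%). All 36 entries of Table 1 reproduce within 2 percentage points, so this is in effect the inflation that the plan uses for clustering by authority.

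**Step 2: effect of leaving the authority out.** With equal numbers of parents per centre, the test of arm in a parents-in-centres model is equivalent to a t test on centre means. If centre means in the same authority correlate at r, the ignored design effect is the DE above with r in place of the ICC. The reported standard error is too small by the factor √DE, and the actual error rate of a nominal 5% test is 2 × (1 − Φ(1.96/√DE)).

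Assumption: r equals the protocol's ICC of 0.05 to 0.1, although that ICC is stated for centre-level enrolment and attrition and not for parent-reported outcomes.

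- r = 0.05: √1.337 = 1.156; standard error 1 − 1/1.156 = 14% too small; 1.96/1.156 = 1.695; error rate 9.0%.
- r = 0.10: √1.675 = 1.294; standard error 1 − 1/1.294 = 23% too small; 1.96/1.294 = 1.515; error rate 13.0%.

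Simulation (6,000 null trials each, 24 authorities, varying numbers of centres with mean 6 and CV 0.54) gave 9.4% and 13.1% for the centre-level test. An unweighted t test of authority means gave 4.7% and 5.2%.

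**Step 3: illustration with parent-level variances.** The protocol states no parent-level ICC and no analysed number of parents per centre. With an authority share a, a centre share c and p parents per centre,

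r = a / (a + c + (1 − a − c)/p).

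Assume p = 8 and c = 0.05:

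- a = 0.01: r = 0.01/(0.06 + 0.1175) = 0.056, error rate 9.5% (simulated 9.7%);
- a = 0.02: r = 0.02/(0.07 + 0.11625) = 0.107, error rate 13.6% (simulated 13.6%);
- a = 0.05: r = 0.05/(0.10 + 0.1125) = 0.235, error rate 22.3% (simulated 22.6%).

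Over p from 6 to 16, a from 0.01 to 0.10 and c from 0 to 0.10, the formula runs from about 8% to 40%. As a approaches 0, it returns to 5%. Across all simulated settings the test on authority means stayed between 4.7% and 5.5%.

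**The case against.** The strongest reply is that the protocol does not plan to draw an arm conclusion from this model. The stated comparison for these outcomes is cluster-level, and the Design section defines the cluster as the authority. The random-effects models are sensitivity analyses whose own reliability is to be examined. Fitting all three structures side by side is a reasonable way to see what each level contributes, and two of the three include the authority. The questionnaire outcomes are presented as exploratory, and a detailed analysis plan is to follow.

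Most of this stands. A reader might infer that the trial's secondary comparisons as a whole run at an inflated error rate, or that a figure above 20% can be read off the protocol. Neither is supported. The planned comparison works at the randomised level. The borrowed ICC gives 9% to 13%, and anything higher needs parent-level variances and parent numbers that the document does not contain. Nor does the text say that the centres-only model would be reported as support for an effect. Degrees of freedom for these models and the random-effect level of the logistic models are details that the article may leave to the analysis plan, and they are not part of this point.

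What does not stand is that examining reliability settles the matter. No criterion for reliability is given. A centres-only model can converge and fit well and still be wrong for the arm effect, because the fault lies in its relation to the allocation. Describing clustering does not need an arm effect from it either: the three-level model in the same sentence supplies variance components for both centre and authority.

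**Conclusion.** The point holds as a minor one about a single named sensitivity model. The centres-only structure omits the unit that was randomised, and an arm effect estimated from it would have too small a standard error whenever authority-level variance is above zero. If the protocol's ICC of 0.05 to 0.1 is carried over as the correlation between centre means, the error rate of a nominal 5% test is about 9% to 13%. That carry-over is an assumption, because the ICC was set for centre-level engagement outcomes. The parent-level scenarios show that the inflation could be smaller or larger and do not estimate it for this trial. The cluster-level secondary analysis, the two structures that include the authority, and the co-primary conclusions are not affected.

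**What to change.** Add one sentence to Secondary analysis, or carry it into the statistical analysis plan: *Any random-effects model used to estimate a difference between arms will include a random effect for local authority, either with parents in authorities or with parents in centres in authorities.* If the centres-only structure is kept, state that it serves only to describe clustering and that no arm effect, confidence interval or p-value will be reported from it.

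No extra data are needed. The cost is wider intervals from this sensitivity analysis than the centres-only model would have shown.

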### Objectives

Primary objectives of the trial are to determine the following:The effect of the optimisation intervention applied to HENRY compared with standard HENRY in regard to increasing parent enrolment in HENRY programmes or reducing parent attrition within HENRY programmesThe willingness to pay of commissioners of the HENRY programme per additional level of parent engagement related to the optimisation intervention (Costs will be presented as an incremental cost per increase of parent engagement, so that commissioners are able to identify the point at which additional costs are acceptably offset by the benefits of engaging effectively with parents.)

Secondary objectives of the study are to determine:The effect of the optimisation intervention on achieving combined parent enrolment, attrition and compliance targetsThe effect of the optimisation intervention on parent compliance with HENRY programme contentThe effect of the optimisation intervention on parent-reported family habits and lifestyleThe potential longitudinal impact (sustainability) of the optimisation intervention on enrolment and attrition in centres that provide data from more than one programme

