### Unit of randomisation

Local authorities will be randomised in a 1:1 allocation ratio (HENRY + optimisation intervention, HENRY as standard) by a statistician at LICTR, using an algorithm for covariate-constrained randomisation [47] to achieve a balanced allocation between the trial arms on (1) local authority baseline level of parental engagement with HENRY (proportion of centres recruiting a minimum of eight parents per programme, proportion of centres retaining at least 75% of parents for a minimum of five of eight sessions), (2) proportion of centres running at least one HENRY programme in 2015, (3) size of local authorities (number of children’s centres participating), and (4) area deprivation (proportion of centres in the least/most deprived quintiles as ranked by the 2015 Index of Multiple Deprivation at the Lower Layer Super Output Area) [48]. Randomisation will be performed for all local authorities at a single time point after baseline data are transferred, prior to the implementation of the intervention. All possible enumerations of allocation to the trial arms will be generated, and an imbalance statistic will be calculated for each allocation. A set of optimal allocations which minimise the imbalance will be provided, and, in accordance with the principles of International Conference on Harmonisation of Technical Requirements for Registration of Pharmaceuticals for Human Use guidance on randomness, the final allocation will be randomly selected from among this optimal set [49]. Results of the randomisation procedure will be sent by the LICTR statistician to the HENRY central office, which will be responsible for informing local authorities of their treatment allocation.

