*Family activity* (via a brief HENRY questionnaire asking parents to report the frequency that parents and children engage in exercise). This questionnaire has been developed bespoke to use within the HENRY evaluations and includes parental report of their own activities that result in breathlessness, with response categories ranging from none to <1 h, 2 h, 3 h or >3 h. Children’s activity is assessed using parental report as energetic play, with response categories ranging from none to 5–15 minutes, 20–30 minutes, 30 minutes to 1 h, or >1 h.
*Child screen time* (via a parent reported using the bespoke HENRY questionnaire). This assesses use of televisions, DVDs, computers, smartphones, and so forth with response categories ranging from none to <1 h, 1–2 h, 2–3 h, or >3 h.
*Intake of key indicator foods per day* (assessed via 14 items from a modified validated Food Frequency Questionnaire [53] completed in relation to the parent and child). Parents are asked to estimate how often (never, once per month, once per fortnight, 1–7 days per week) they consumed each of the 14 items or groups of foods (e.g., fresh fruit, sweets, chocolate, water), with space to report the number of times consumed. It has previously demonstrated sensitivity to change with parents attending HENRY sessions [25].
Longitudinal impact of HENRY + optimisation intervention vs HENRY alone (parent engagement [enrolment and attrition] within centres during the 12-month follow-up in local authorities which provide data for more than one programme per centre at follow-up) (This evaluation will explore whether the optimisation intervention needs time to ‘bed-in’ and/or whether any early effects are maintained over time.)

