### Data collection and transfer

In this trial, we will use routinely collected data for all primary and secondary outcomes, except for the process evaluation data, which will be gathered by an independent LICTR researcher. HENRY has designed a centralised process for evaluating programmes, developed for QA purposes and reporting to commissioners of the service. For the purpose of this trial, baseline data at the centre level include routine data on enrolment and attendance at programmes that have been run before randomisation. These data also include anonymous information on participant satisfaction, parent-reported compliance, parenting and family lifestyle (Table 2), which are gathered in questionnaires on the first and last days of each HENRY programme. This information is submitted to the central HENRY office (without any personal identifiers for the families), which check the data for completeness and collate the information in a.csv file.

**Table 2 Tab2:** Data collection summary

Data	Screening	Randomisation	Baseline	On-going	Follow-up
Local authority level					
Cluster eligibility	X				
Stratification factors		X			
Programme enrolment			X		X
Programme attrition			X		X
Implementation data (e.g., fidelity)				X	
Parent level (anonymised routine)					
Infant diet (fruit and vegetable intake)			X		X
Family habits and lifestyle			X		X
Implementation/process data				X	
Intervention level					
Costs for intervention delivery for economic evaluation	X	X	X	X	X

X indicates when data are gathered

For the trial period, centre-level baseline data from the most recent programme delivered prior to randomisation (winter term 2015) will be used. Follow-up data will be gathered 12 months after randomisation. It will include routine data collected from the autumn and spring terms (2016–17), allowing 6 months for intervention delivery at all sites followed by the delivery of two terms of HENRY programmes. In accordance with the planned intention-to-treat (ITT) analysis, data will be collected from centres that are not compliant with the intervention. For those withdrawing from the trial, only data collected up to the point of withdrawal will be used.

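### The longitudinal model adjusts for programme time point but names no arm-by-time contrast, so as written it cannot tell whether the effect beds in, fades or stays constant

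*Protocol article*

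**What the plan says.** The Objectives section of the Protocol article lists, as a secondary objective, the potential sustainability "of the optimisation intervention on enrolment and attrition in centres that provide data from more than one programme". The Secondary outcomes section explains the purpose: to explore whether the optimisation takes time to bed in, and "whether any early effects are maintained over time".

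The Secondary analysis section gives the method. Longitudinal impact on engagement is to be estimated "using logistic regression with random effects adjusting for the time point of the programme". Only part of the trial enters this model: it is run "among those local authorities providing data for more than one programme per centre at follow-up". The section mentions no interaction between arm and time and no effect by term.

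Three other statements bear on this:
- Follow-up uses "routine data collected from the autumn and spring terms" of 2016–17 (Data collection and transfer), so there are two time points.
- "Local authorities will be randomised in a 1:1 allocation ratio" (Unit of randomisation).
- "Statistical analyses will be carried out by the ITT principle, and statistical significance will be assessed at the two-sided 5% significance level" (Analysis).

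**The concern.** Bedding-in means a small arm effect in autumn and a larger one in spring. Fading means the reverse. Both describe a difference between two arm effects. A model with arm and time as main effects contains no such quantity. Adjusting for time removes a trend assumed common to both arms and leaves one arm odds ratio for both terms. If the SAP carries the sentence over unchanged, the sustainability objective will be reported through a single coefficient that does not address it.

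A second, smaller matter is the analysis set. Whether a site supplies repeat programmes is known only after randomisation, and an intervention that supports authorities, centres and facilitators could affect it. The article also sets the condition at two levels: centres in Objectives, authorities in Secondary outcomes and Secondary analysis. It does not say whether a single-programme centre in a qualifying authority stays in.

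**Working it through.** **The plan's own figures.** The article gives no power or sample size for the longitudinal analysis. Table 1 concerns one result per centre. It reproduces: the design effect at ICC 0.05 is 1 + ((1 + 0.54²) × 6 − 1) × 0.05 = 1.337, so the effective number per arm is 72 / 1.337 = 53.8. Power for 55% versus 80% is then 79.9% (stated 79%). All 36 cells agree within 2 points. Table 1 is not at issue and says nothing about a repeated-programme model.

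**Inputs for the check.** Two terms (Data collection and transfer) and a control enrolment rate of 55% (Sample size), held flat over both terms. The three effect patterns are my assumptions:
- bed-in: intervention 55% in autumn, 80% in spring
- fade: intervention 80% in autumn, 55% in spring
- constant: intervention 69% in both terms

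**Term-specific log odds ratios.**
- 80% versus 55%: ln[(0.80/0.20) / (0.55/0.45)] = ln(3.273) = 1.19
- 55% versus 55%: 0
- 69% versus 55%: ln[(0.69/0.31) / (0.55/0.45)] = ln(1.821) = 0.60

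The interaction (spring minus autumn) is therefore +1.19 for bed-in, −1.19 for fade and 0 for constant.

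**What the main-effects model returns.** Let logit(p) = a + b·arm + t·spring, with equal numbers per cell and clustering ignored. Maximum likelihood matches the arm totals and the term totals. For bed-in:
- control total 0.55 + 0.55 = 1.10; intervention total 0.55 + 0.80 = 1.35
- autumn total 0.55 + 0.55 = 1.10; spring total 0.55 + 0.80 = 1.35

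The two sets of totals are equal, so t = b. Writing expit for the inverse logit, the equations are expit(a) + expit(a + b) = 1.10 and expit(a + b) + expit(a + 2b) = 1.35. The solution is a = −0.065 and b = 0.539. For fade, swapping the terms gives the same b = 0.539 with t = −0.539.

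| Pattern | Arm log-OR, time adjusted only | Time coefficient | Arm-by-term interaction |
|---|---|---|---|
| Bed-in | 0.54 | +0.54 | +1.19 |
| Fade | 0.54 | −0.54 | −1.19 |
| Constant | 0.60 | 0 | 0 |

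Only the time coefficient differs between bed-in and fade, and the model shares it between arms. For bed-in the fitted control rates are 48% then 62%, although the true rates are 55% in both terms. A reader would take this for a calendar trend common to both arms.

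**Check with clustering.** A simulation used 24 authorities × 6 centres × 2 terms, authority ICC 0.05, an assumed centre ICC of 0.10, and 1,000 runs. It fitted a logistic model with cluster-robust standard errors in place of random effects. The time-adjusted arm log odds ratios were 0.52, 0.55 and 0.60; the interactions were +1.18, −1.20 and 0.01. Power for the interaction was about 70% for the 25-point swing if all 144 centres ran in both terms. It rejected in 6.3% of runs when the effect was constant. Power would be lower in a retained subset.

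**The restriction.** With a true effect of zero, an illustrative selection model gave no apparent difference when repeat running depended on centre engagement equally in both arms. When it depended on engagement in one arm and not the other, the apparent difference was −5.6 to −9.0 points. The strength of selection is assumed, so this shows a possible mechanism and is not an estimate for this trial.

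**The case against.** **The model is given in one sentence and an SAP is to follow.** The sentence does not list arm as a term either, and the Analysis section promises review and a detailed SAP before formal analysis. This stands in part: the absence of an interaction is inferred from silence, and the SAP may contain one. But the article does say what is done with time, and adjusting for it is not the contrast that its stated purpose needs.

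**The subset is the declared question.** The objective is framed in sites with repeat programmes, and a centre with one programme carries no within-centre information on change. Bringing such centres in lets differences between autumn-only and spring-only centres enter the term contrast. This stands, so the subset should be kept and a wider analysis set beside it.

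**A reader might infer that the restriction breaks the randomised comparison.** The documents do not support that. Selection is possible, but its size is unknown and it is nil if it acts alike in both arms. The set of centres with at least one follow-up programme is also defined after randomisation; it reduces the selection without removing it.

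**A reader might also infer that most of the data are thrown away.** Take 150 programmes a year (Background, where it is a floor), 144 centres, and two of three equal terms. The mean is then 150/144 × 2/3 = 0.694 programmes per centre. If counts are Poisson:
- centres with two or more: 1 − e^(−0.694) × 1.694 = 15%
- among centres with any programme: 0.154 / 0.501 = 31%
- share of programmes that lie in such centres: 1 − e^(−0.694) = 50%
- authorities of six centres with at least one such centre: 1 − 0.846⁶ = 63%

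So about half of programmes are kept even on the centre reading, and the Secondary analysis section restricts by authority. Neither equal terms nor Poisson counts are stated in the article.

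**The stakes are modest.** The outcome is secondary and exploratory, and neither the co-primary analyses nor the effectiveness criterion depends on it. This stands.

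**Conclusion.** The point holds for the model. The stated purpose needs a change in arm effect over time, and the stated method, read as written, estimates an average over two terms. In the worked example opposite patterns give the same arm estimate (0.54) and lie close to a constant effect (0.60), while the interaction separates them by more than two units of log odds ratio (+1.19 against −1.19). The exact values rest on the assumed patterns and a flat control rate. That a main-effects model contains no arm-by-time contrast rests on neither.

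On the analysis set the conclusion is narrower. The condition is declared, is observed after randomisation, and is stated at two different levels. It may introduce selection of unknown size. No bias has been shown, and the documents do not fix how much data would be lost. The change should be made, but nothing here threatens the primary conclusions.

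**What to change.** In the SAP, and in the article's description of the method:
1. Fit arm, term (autumn/spring) and arm-by-term, with random effects for authority and centre. Report the arm effect in each term and the interaction, each with a 95% confidence interval, and label the analysis exploratory.
2. State whether the repeat-programme condition applies to centres or to authorities, and word Objectives, Secondary outcomes and Secondary analysis alike.
3. Report the number of programmes run per centre by arm, so that readers can judge selection.
4. Add an analysis of all randomised centres with at least one follow-up programme beside the repeat-programme subset, noting that this set too is defined after randomisation.

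The cost is one model term, one extra analysis and one table. No new data are needed. The drawback is precision: even a 25-point swing has only about 70% power in the best case simulated, so a non-significant interaction must not be read as evidence that the effect was maintained.
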